#### 4) Frequency of rescue drug usage

Check the subjects medicated with rescue drugs each visit after administering the investigational products to suggest rescue drugs usage rate and perform the chi-square test or the Fisher's exact test to compare the rescue drug rates between each group followed by the t-test to check for difference in total usage amount between groups.

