| Confirmation of pain reliever administration stoppage        |                             | X                     |         |         |
| Random assignment                                            |                             | X                     |         |         |
| 100mm Pain VAS assessment                                    | X                           | X                     | X       | X       |
| K-WOMAC assessment                                           |                             | X                     | X       | X       |
| Patient Global Assessment                                    |                             |                       | X       | X       |
| Adverse events                                               |                             |                       | X       | X       |
| Confirmation of change in co-administered drugs  |                             |                       | X       | X       |
| Prescription of investigational product                      |                             | X                     | X       |         |
| Rescue drug prescription and distribution of rescue drug log | X                           | X                     | X       |         |
| Survey on frequency of rescue drug usage                     |                             | X                     | X       | X       |

- 
- 1 For subjects administered and treated with non-steroid anti-inflammatory pain reliever, osteoarthritis supplements, physical therapy, and oriental therapy(Acupuncture, cupping, moxibustion) within 2 weeks prior to screening must stop such administration and treatment for 14 days for a washout period and subjects without administration and treatment within the past 2 weeks can be administered with investigational products without having a washout period.
  - 3 It can be substituted with test results within 3 months from screening date.
  - 4 It can be substituted with test results within 4 weeks from screening date.

|                      |                                                                                                                                                                                     |
|----------------------|-------------------------------------------------------------------------------------------------------------------------------------------------------------------------------------|

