##### **4.1.1.4 Frequency of Rescue drug Usage**

Check for ratio and amount of medication among subjects by checking administration of rescue drug distributed to subjects upon every visit excluding visit 1.

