## **4.2 Procedure by Visit**

### **4.2.1 Visit 1(Screening and Washout Period, 14 Days Prior to Trial)**

Subjects selected for participation in this study shall be evaluated according to following sequence after listening to description of the study.

- 1) Describe trial procedure to subject and receive written consent form from subject prior to participation.
- 2) Assign screening number to subject in sequence of consent.
- 3) Survey and record demographic data and medical/medication history(Past and current history including surgeries).
- 4) Measure vital signs and weight and conduct physical examination.
- 5) Measure weight.
- 6) Conduct laboratory tests(Hematologic test, blood chemistry test, urine test, blood coagulation test).
- 7) Conduct pregnancy test for female subjects of childbearing age.
- 8) Perform ECG.
- 9) Conduct x-ray examination.
- 10) Evaluate according to ACR diagnosis criteria.
- 11) Evaluate according to inclusion/exclusion criteria.
- 12) Stop administration if subject is being regularly medicated with pain reliever and such and train on the washout period over 3~14 DAYS.

- 13) Evaluate 100mm Pain VAS.
- 14) Prescribe rescue drug.
- 15) Train on rescue drug log writing and distribute rescue drug log.
- 16) Schedule next visit.

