#### **7.2.4.1 Primary Effectiveness Analysis**

- Change in 100mm Pain VAS on 28th day compared to baseline

Calculate the upper limit(97.5% one-sided confidence interval) for 95% two-sided confidence interval for the difference in change of 100mm Pain VAS on the 28th day compared to baseline of test and control groups(Average change in test group - Average change in control group). If the upper limit of the confidence interval is below 15mm, then it shall be determined that the test group is not inferior compared to the control group. For this, configure the change in 100mm Pain VAS as dependent variable with the administration group as the random factor, and the baseline 100mm Pain VAS as the covariate to perform the covariance analysis. Suggest the calibrated average for the change in 100mm Pain VAS for each administration group based on this analysis and suggest the difference in calibrated means between the two group and its 95% confidence interval.

Additionally, mean, standard deviation, minimum and maximum values shall be suggested for the amount of 100mm Pain VAS measured at each visit for the test group and the control group and the change in 100mm Pain VAS on the 28th day compared to baseline.

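### Rescue use before dosing is scheduled to be recorded, but on-treatment rescue amount is compared by an unadjusted t-test, which gives up some precision on one secondary variable

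*Protocol*

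**What the plan says.** **Collection before dosing.** The Clinical Trial Schedule marks "Rescue drug prescription and distribution of rescue drug log" at Visits 1, 2 and 3, and "Survey on frequency of rescue drug usage" at Visits 2, 3 and 4. Section 4.2.1 lists at Visit 1 "Train on rescue drug log writing and distribute rescue drug log", with no condition on whether the subject needs a washout. Section 4.1.1.4 describes the measure as obtained "by checking administration of rescue drug distributed to subjects upon every visit excluding visit 1". Visit 2 is the randomisation and first-dose visit, so what is checked there is use before treatment.

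**Analysis.** Section 7.2.4.2 item 4 restricts the analysis to the treatment period: "Check the subjects medicated with rescue drugs each visit after administering the investigational products". Usage rates are compared by chi-square or Fisher's exact test, "followed by the t-test to check for difference in total usage amount between groups". No covariate is named and the Visit 2 record has no role.

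**Contrast.** For VAS change at Day 28, Section 7.2.4.1 uses "baseline 100mm Pain VAS as the covariate to perform the covariance analysis", and Section 7.2.4.2 item 1 applies the same method at Day 14.

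**General rule.** Section 7.2.3 allows a baseline variable to enter as a covariate, or to be handled by subgroup analysis, when the arms differ on it and the difference is judged relevant to the effectiveness variable.

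**The concern.** How much acetaminophen a subject takes plausibly reflects habit as well as current pain. Use before dosing is therefore a candidate predictor of use on treatment, and adjusting for it would tighten the comparison even when the arms are balanced. The protocol already follows this principle for VAS but not for rescue amount, although a pre-dose value is scheduled for both.

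Precision matters here because rescue drug is allowed in both arms while the primary analysis tests non-inferiority on VAS. If one arm takes more rescue drug, VAS scores may be drawn together. Section 7.2.4.2 item 4 is the planned between-arm check on that, and in such a check an imprecise, non-significant result can be misread as reassurance.

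**Working it through.** **1. The plan's own figure.** Section 3.2.2 gives SD 24.86 mm, margin 15 mm in absolute value, one-sided alpha 0.025 and power 0.975. Then n = 2 × 24.86² × (1.96 + 1.96)² / 15² = 84.41, rounded up to 85 per arm. With 10% dropout, 85 / 0.9 = 94.4, rounded up to 95. Both stated figures reproduce. They concern VAS only; the protocol gives no SD, effect size, power or correlation for rescue use.

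**2. What the planned t-test can detect.** With 85 per arm and two-sided alpha 0.05 (Section 7.2.2), the standardised difference detected with 80% power is (1.960 + 0.842) × √(2/85) = 0.430.

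**3. Effect of adjustment.** Two quantities are assumptions:
- r: the correlation between the recorded pre-dose daily rate and on-treatment use, among subjects with a record.
- w: the share of subjects with a pre-dose record.

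Taking the outcome variance as similar with and without a record, linear adjustment multiplies the residual variance by 1 − w·r² and the confidence interval width by √(1 − w·r²). Power is taken at the difference of 0.430, where the unadjusted test has 80%.

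| w | r | Variance factor | CI width factor | CI narrower by | Equivalent unadjusted n per arm | Power |
|---|---|---|---|---|---|---|
| 1 | 0.3 | 0.910 | 0.954 | 4.6% | 93.4 | 83.6% |
| 1 | 0.5 | 0.750 | 0.866 | 13.4% | 113.3 | 89.9% |
| 1 | 0.6 | 0.640 | 0.800 | 20.0% | 132.8 | 93.8% |
| 0.5 | 0.3 | 0.955 | 0.977 | 2.3% | 89.0 | 81.8% |
| 0.5 | 0.5 | 0.875 | 0.935 | 6.5% | 97.1 | 85.0% |
| 0.5 | 0.6 | 0.820 | 0.906 | 9.4% | 103.7 | 87.2% |

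Example: w = 0.5 and r = 0.6 give 1 − 0.5 × 0.36 = 0.82, and √0.82 = 0.906.

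**4. Who has a pre-dose record.** Section 3.1 lets some subjects skip the washout, in a proportion not stated. The Visit 1 steps for rescue prescription and the log carry no washout condition, whereas the step on stopping pain relievers applies only to subjects taking them regularly. A subject without a washout can therefore still have a Visit 1 to Visit 2 record if the visits fall on different days. So w is not simply the share with a washout.

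**5. Quality of the pre-dose rate.** Sections 3.1, 4.2.1 and 4.2.2 give a washout of 3 to 14 days (footnote 1 of the schedule says 14), and Section 6.7.1 bars rescue drug in the 24 hours before a visit. A 3-day interval then leaves about two days of possible use. Unequal intervals make raw counts non-comparable, so a per-day rate is needed, and short intervals make that rate noisy, which lowers r.

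**The case against.** The strongest reply is that nothing here is an error. The two-sample t-test is valid under randomisation, rescue use is the fourth-listed secondary variable, and the choice of covariates is often settled in a statistical analysis plan, which is not available here. The point about validity stands in full. The point about the analysis plan stands in part: the protocol does not forbid adjustment, but it names the test itself and gives the Visit 2 record no use.

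A reader might infer that the pre-dose data are simply discarded. That goes too far, because Section 7.2.3 leaves a route for baseline covariates. But that route opens only on an observed imbalance, so it neither prespecifies the adjustment nor delivers the precision gain when the arms are balanced.

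A reader might also infer that the planned comparison is likely to miss a real difference in rescue use. The documents do not support this: they state no expected difference, and the planned test has 80% power at 0.43 SD.

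Finally, pre-dose rescue use is a weaker baseline than baseline VAS. It covers short, unequal intervals and, for many subjects, withdrawal from earlier analgesics rather than treatment with an active NSAID. This stands, and is a reason to expect a modest correlation. Visit 2 recording also rests on the schedule and Section 4.1.1.4, since the list in Section 4.2.2 does not clearly name the rescue survey.

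**Conclusion.** The point holds as a minor efficiency gain. A pre-dose rescue measure is scheduled, the stated analysis of rescue amount does not use it, and the general covariate rule depends on observed imbalance. The cost is precision on one secondary variable. There is no bias and no inflation of type I error. A reader might infer that the non-inferiority conclusion is at risk; it is not, because the decision in Section 7.2.4.1 rests on the VAS confidence interval alone.

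The size cannot be fixed from the documents. Under an assumed r of 0.3 to 0.6, the interval narrows by about 5% to 20% if all subjects have a pre-dose record and by about 2% to 9% if half do. Both r and w are assumptions, and the noise in the pre-dose rate argues for the lower part of these ranges.

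**What to change.** In Section 7.2.4.2 item 4, replace the t-test on amount with a prespecified linear model:

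- **Outcome:** on-treatment rescue tablets per day. State openly that this replaces total amount as the compared quantity, and keep total amount as a descriptive result.
- **Terms:** treatment; pre-dose rescue tablets per day from the Visit 1 to Visit 2 log; and an indicator for subjects with no Visit 1 to Visit 2 interval or no record.
- **Rule for the covariate:** use the actual record for every subject who has one, with or without a washout. Set the covariate to a constant only where no record exists. Assigning zero to everyone without a washout could overwrite real data.

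The comparison of usage rates can stay as planned. The cost is a few sentences before unblinding, with no new visits or data. The downside is that the pre-dose rate is noisy, so the gain may be small.

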#### **4.2.4 Visit 4(End of Clinical Trial, Day 28±3)**

This visit takes place on the last day of the study for final effectiveness evaluation of subjects administered investigational products for 28 days. Also, the following items are evaluated even if the clinical trial ends prematurely.

- 1) Check for changes in co-administered drugs compared to previous visit.
- 2) Investigate for occurrence of adverse events and its details.
- 3) Measure vital signs and weight and conduct physical examination.
- 4) Conduct laboratory tests(Hematologic test, blood chemistry test, urine test).
- 5) Conduct pregnancy test for female subjects of childbearing age.
- 6) Perform ECG.
- 7) Evaluate 100mm Pain VAS.
- 8) Evaluate K-WOMAC.
- 9) Evaluate Patient Global Assessment.
- 10) Recover residual clinical trials from the subject and record residual quantity.

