### **7.2 Plan for Statistical Analysis**

#### **7.2.1 Definition of Analysis Sets**

Analysis sets are defined as below.

- (1) Safety analysis set: It consists of randomly assigned subjects who have been medicated with investigational products at least once.
- (2) FAS (Full Analysis Set): It consists of subjects that yield data on primary effectiveness evaluation variables who have been medicated with investigational products at least once.
- (3) PPS (Per-Protocol Set): It consists of subjects who completed the trial according to the clinical trial plan among subjects included in the FAS.

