#### **7.2.2 General Statistical Principles**

Verification of all statistical significance shall be performed by a two-tail test

with significance level( $\alpha$ ) of 5%. However, noninferiority will be verified using the confidence interval.

Main analysis of data regarding effectiveness from subjects of this clinical trial shall be performed through PPS followed by additional analysis of FAS by principle.

Analysis of data regarding safety shall be performed through the safety analysis set.

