#### **7.2.6 Processing of Dropout or Missing Values**

The most recent data will be used for data analysis as if it was obtained at the corresponding point in time(Last Observation Carried Forward Method) should the subject is disqualified due to dropout or there is a missing value in data during FAS analysis before the clinical trial ends.

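### In the additional FAS analysis, comparing raw total rescue use without allowing for days observed can understate use in the arm with more early leavers

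*Protocol*

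**What the plan says.** Frequency of rescue drug usage is the last of the four secondary effectiveness variables (Protocol 7.1.2). Collection is described in 4.1.1.4: "Check for ratio and amount of medication among subjects by checking administration of rescue drug distributed to subjects upon every visit excluding visit 1". The analysis in 7.2.4.2 item 4 has two parts. For the share of users, the plan is to "perform the chi-square test or the Fisher's exact test to compare the rescue drug rates between each group". For the amount, it is a "t-test to check for difference in total usage amount between groups". None of these places gives a denominator of days or of visit intervals.

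Three other provisions bear on this.

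- Analysis sets (7.2.1, 7.2.2). The main effectiveness analysis "shall be performed through PPS followed by additional analysis of FAS by principle". Of the PPS the protocol says "It consists of subjects who completed the trial according to the clinical trial plan among subjects included in the FAS"; of the FAS, "It consists of subjects that yield data on primary effectiveness evaluation variables who have been medicated with investigational products at least once".
- Early termination (4.2.4). At Visit 4, "the following items are evaluated even if the clinical trial ends prematurely", so an early leaver can have a last pain score and thereby belong to the FAS.
- Missing data (7.2.6). In the FAS, "The most recent data will be used for data analysis as if it was obtained at the corresponding point in time". The rule is general and does not say how it works for an amount that accumulates over time.

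**The concern.** A total is a daily rate multiplied by the days over which it was counted. A subject who leaves at mid-trial has about half the time in which to take rescue tablets, so the total is smaller at the same daily need. If one arm loses more subjects early, its mean total falls for a reason unrelated to pain control. Those who leave because of poor relief may well be heavier users, though the protocol gives no data on that. The variable is there partly to show whether one arm leans more on rescue, and in the FAS the raw total can blunt that signal in the arm where it matters most.

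**Working it through.** **Inputs from the protocol.** 95 randomised and 85 evaluable per group, 10% dropout overall (3.2); Visit 4 at Day 28±3 (4.2.4); two-sided 5% tests (7.2.2). The protocol gives no rescue rate, no spread of rescue use and no dropout by arm; these are assumed below and shown as ranges.

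**The plan's own figure.** The only figure is the sample size for the primary endpoint: 2 × 24.86² × (1.96 + 1.96)² / 15² = 84.4, so 85; 85 / 0.90 = 94.4, so 95. Both reproduce, and neither involves rescue use.

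**Excess cancelled by early leaving (FAS, no LOCF).** Let d be the share who leave and f the fraction of the 28 days they reach. If leavers use rescue at the same daily rate as others in their arm, mean days observed are proportional to 1 − d(1 − f). Then:

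ratio of mean totals = true rate ratio × [1 − d_T(1 − f)] / [1 − d_C(1 − f)]

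The true excess that is exactly cancelled is the inverse of the bracketed ratio, minus 1. For 5% versus 15% and f = 0.5: 0.925 / 0.975 = 0.949, and 1 / 0.949 − 1 = 5.4%.

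| Dropout, control vs test | f = 0.75 | f = 0.50 | f = 0.25 |
|---|---|---|---|
| 10% vs 10% | 0% | 0% | 0% |
| 5% vs 15% | 2.6% | 5.4% | 8.5% |
| 0% vs 20% (extreme) | 5.3% | 11.1% | 17.6% |

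All three rows average the protocol's 10%.

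**Simulation.** 95 per arm, 1,500 runs per scenario. Assumed: control mean 0.5 tablets/day, gamma-Poisson counts with shape 0.5, leavers out at Day 14, completers observed 25 to 31 days, no LOCF. Entries are the mean difference in tablets over 28 days, with the chance that a t-test detects the worse arm in brackets (simulation error about 1.3 percentage points near 45%).

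| Rate ratio; dropout | Raw total | Per day observed, ×28 | Completers only, raw total |
|---|---|---|---|
| 1.10; 0% vs 20% | −0.16 (1.8%) | 1.38 (6.1%) | 1.36 (6.0%) |
| 1.25; 5% vs 15% | 2.47 (11.1%) | 3.43 (16.3%) | 3.45 (15.8%) |
| 1.50; 10% vs 10% | 6.48 (43.9%) | 6.80 (45.2%) | 6.84 (40.5%) |
| 1.50; 5% vs 15% | 5.77 (36.2%) | 6.99 (47.6%) | 6.98 (43.9%) |
| 1.50; 5% vs 15%, leavers use twice as much | 7.01 (47.0%) | 9.50 (59.5%) | 6.98 (42.4%) |
| 1.50; no dropout, window only | 6.98 (47.3%) | 6.99 (47.1%) | 6.98 (47.3%) |

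At equal dropout the ratio of totals is right; the absolute difference shrinks slightly because both arms lose the same share of days.

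**Visit window.** 25/28 = 0.893 and 31/28 = 1.107, so one subject's total moves by at most 10.7%. The last row shows no bias when the window is alike in both arms.

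**LOCF, two readings.** Take an assumed case: completers use 1 tablet/day for 28 days, and leavers use 2 tablets/day and go at Day 14, with 5% versus 15% leaving. True daily means are 0.95 + 0.10 = 1.05 and 0.85 + 0.30 = 1.15, a ratio of 1.095.

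- Carry the total forward: a leaver keeps 28 tablets, and both arms average 28.0. The difference is gone.
- Carry the last interval into the missing one: a leaver counts 28 + 28 = 56. The means are 0.95 × 28 + 0.05 × 56 = 29.4 and 0.85 × 28 + 0.15 × 56 = 32.2, a ratio of 1.095, which is the true one.

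The second reading works here because the leaver has completed a full first interval. Someone who goes before Visit 3 has no earlier on-treatment interval to carry, and a partial interval could be carried as if it were whole.

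**The case against.** The strongest reply is that the main rescue comparison is made in completers, so truncated totals never enter it. That stands, and it confines the problem to the additional FAS analysis. It does not remove it: 7.2.2 calls for the FAS analysis, and only that set can show rescue use among subjects who left. With leavers using twice as much, the completer analysis shows 6.98 tablets against 9.50 per day observed, scaled to 28 days. Leaving them out of the PPS is a separate selection question, which a days denominator would not cure.

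A reader might also infer that short visit intervals hide a worse arm. The documents do not support this. The window is the same for both blinded arms, and the schedule's allowance for moving a visit after recent analgesic use would more plausibly lengthen an interval than shorten it.

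A reader might infer that LOCF cannot repair a total. That is too strong, as the per-interval reading shows. What stands is that 7.2.6 does not say which reading applies.

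The complete loss of the difference in the worked example should not be taken as typical. Two tablets for 14 days equals one tablet for 28, so the raw totals match at any dropout rates.

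Finally, amounts may well be skewed with many zeros, but at 85 to 95 per arm that alone does not make a comparison of means wrong. Preferring a rank test would be a matter of taste. The share of users is compared as well, though it does not measure amount.

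**Conclusion.** The concern holds in a limited form. The protocol itself fixes a raw total without a days denominator, so this is not merely detail left to an SAP. In the FAS, and only if early leaving differs by arm, the total understates rescue use in the arm with more leavers. At 5% versus 15% dropout the cancelled excess is 2.6% to 8.5%; at a rate ratio of 1.5 most of the difference survives (5.77 against 6.99 tablets), with detection falling from about 48% to 36%. At equal dropout no excess is cancelled. The sizes rest on assumed rescue rates, spread, leaving times and dropout split, and on FAS totals being taken without a per-interval LOCF.

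It would go beyond the documents to say that the main rescue analysis is biased or that the trial's conclusion is at risk. Rescue use is secondary; the non-inferiority decision and the 85/95 sample size do not depend on it. This is a cheap improvement to a secondary analysis.

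**What to change.** In 7.2.4.2 item 4, replace the raw total by rescue tablets per day observed: the total taken from Visit 2 to the last visit, divided by the days between them. Alternatively, use a count model with log days observed as offset. Apply it in both PPS and FAS, and state in 7.2.6 that it takes the place of LOCF on the total.

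No new data are needed: rescue use is surveyed at Visits 2 to 4 in the schedule, returned rescue quantities are recorded under 6.6, and visit dates are known. The cost is one line of derivation. The downside is that a subject's rate is noisier when follow-up is short; the offset model eases this by giving such subjects less weight. Either version describes use while under observation, not what leavers would have taken afterwards.
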